**Fig. 1 Fig1:**
[figure not shown]
Participant Timeline (SPIRIT Figure)

## Intervention description {11a}

### Treatment 1: reminders

#### Arm 1R

Participants in the reminder arm with expiration dates during the intervention period will be targeted with the following SMS messages sent to their phone number at the specified intervals before their individual expiration dates.

**Table Taba:** 

Message #	1	2	3	4	5	6
t_x_	t_−28_	t_−7_	t_0_	t_+30_	t_+60_	t_+89_
Condition	Membership has not been renewed by t_x_					
Message	Dear Firstname Lastname, Your NHIS card will expire in *4 weeks*. You can renew using the MyNHIS app, *929# or go to the nearest NHIA district office	Dear Firstname Lastname, Your NHIS card will expire in *1 week*. You can renew using the MyNHIS app, *929# or go to the nearest NHIA district office	Dear Firstname Lastname, Your NHIS card expires *TODAY*! You can renew using the MyNHIS app, *929# or go to the nearest NHIA district office	Dear Firstname Lastname, Your NHIS card is expired. You can renew within 60 days to avoid a 1-month wait. Use MyNHIS app, *929# or go to the NHIA district office	Dear Firstname Lastname, Your NHIS card is expired. You can renew within 30 days to avoid a 1-month wait. Use MyNHIS app, *929# or go to the NHIA district office	Dear Firstname Lastname, Your NHIS card is expired. You can still renew today to avoid a 1-month wait. Use MyNHIS app, *929# or go to the NHIA district office

#### Arm 2R

Members with already expired insurance only receive the following renewal reminder twice.

**Table Tabb:** 

Message #	7
Day of trial	Day 1 and Day 30 of Trial
Condition	Membership has expired and has not been renewed
Message	Dear Firstname Lastname, Your NHIS card expired dd/mm/yyyy. You can use the MyNHIS app, *929# or go to the NHIA district office to renew your coverage

#### Treatment 2: Autorenewal

All participants in these arms will receive Message 1 on Day 1 and Day 30 of trial (if they have not yet signed up). By dialing the short-code *929*20#, participants will be directed to a USSD-Menu where they can opt into the autorenewal service by providing their member number and then authorizing the automatic payment from their MoMo account to the NHIS when the renewal become due. A participant can also add the member number of any other individual (e.g., spouse or child) who they wish to add to the renewal plan.

#### Arm 1 A, 2 A, 3A

**Table Tabc:** 

Message #	8
Day of Trial	Day 1 and Day 30 of trial
Condition	Member has not opted into autorenewal
Message	Dear Firstname Lastname, NHIA offers a new option to renew your membership automatically. You can opt-in by dialling *929*20#. For more information, call NHIA call center at [name]

Once signed up, individuals in arm 1 A will receive messages 2 and 3 on the indicated days, provided that membership has not yet been renewed otherwise. The automatic renewal is triggered 30 days before the expiration date. If the expiration date is less than 30 days away or the membership is already expired, it will be triggered the day after sign-up. If no payment or further documentation is required, insurance is renewed immediately. If a payment is required, it will be debited to the MoMo account of the participant. If payment is successful, the insurance is renewed. If payment is unsuccessful, the member is informed and the renewal will be triggered in the 3 subsequent days again. After that, the member will receive a final message suggesting they attempt renewal via one of the other platforms.

#### Arm 1A

**Table Tabd:** 

Message #	9	10	11	12
t_x_	t_−90,_ t_−60_	t-_31_	t_−30, t-29, t-28,_	t_−27_
Condition	Member has opted into autorenewal. Active membership has not been renewed. The member is required to pay premium or processing fee		Autorenewal payment has failed	Autorenewal payment has failed 4 times
Message	Dear Firstname Lastname, your NHIS insurance automatically renews on dd/mm/yyyy. Please make sure you have xx cedis in your MoMo account (Dial *929*20# to change your settings)	Dear Firstname Lastname, your NHIS insurance automatically renews in one day. Please make sure you have xx cedis in your MoMo account (Dial *929*20# to change your settings)	Dear Firstname Lastname, unfortunately, your membership could not be renewed. We will try again tomorrow. Please make sure you have xx cedis in your MoMo account (Dial *929*20# to change your settings)	Dear Firstname Lastname, your membership could not be renewed automatically Please use MyNHIS app, *929# or go to the nearest NHIA district office

#### Arm 1 A, 2 A, 3A—if expiration is 30 days or less away on day of opt-in (or already expired)

**Table Tabe:** 

Message #	11	12
Condition	Autorenewal payment has failed	Renewal has failed 4 times
Day of sign-up/opt-in (s_0_)	s_+1_, s_+2_, s_+3_	s_+4_
Message	Dear Firstname Lastname, unfortunately, your membership could not be renewed. We will try again tomorrow. Please make sure you have xx cedis in your MoMo account (Dial *929*20# to change your settings)	Dear Firstname Lastname, your membership could not be renewed automatically Please use MyNHIS app, *929# or go to the nearest NHIA district office

#### Criteria for discontinuing or modifying allocated interventions {11b}

Participants can opt out from receiving SMS messages from the NHIA and not receive further communication at any time. Opt-out requests and sign-up rates to the autorenewal system will be monitored intermittently as indicators of protocol adherence and as warning signs of any unforeseen problems. Changes to the protocol may be made if adverse effects on participants or technological faults which threaten the validity of the trial are discovered.

#### Strategies to improve adherence to interventions {11c}

In order to reduce technological and logistical barriers, the NHIS Helpline and local NHIA office staff will be trained to answer questions about the autorenewal system and assist with enrolment if needed.

Individuals with a phone number shared by more than 5 people are excluded from the trial in order to prevent excessive messaging to a single number, which would increase likelihood of opting out.

#### Relevant concomitant care permitted or prohibited during the trial {11d}

There are no requirements or restrictions on care or other interventions for individuals during the duration of this trial.

#### Provisions for post-trial care {30}

We do not expect any potential for harm from reminder messages or the automatic renewal option. However, should any problem occur, the NHIS members support services will be able to assist with any potential issues (Fig. 2).

**Fig. 2 Fig2:**
[figure not shown]
Sample composition and randomization

## Outcomes {12}

### Primary outcome

**Table Tabf:** 

Outcomes	Analysis Metric	Method of aggregation	Time point
Renewal status at end of observation period (renewal by expiration date, renewal without coverage gap, any renewal)	Odds Ratio between treatment and control group for each arm	Proportion succeeding in renewing insurance coverage by date	End of observation period

### Secondary outcomes

**Table Tabg:** 

Outcomes	Analysis Metric	Method of aggregation	Time point
Renewal by expiration date (by t_0_), renewal without coverage gap (by t_90_)	Odds ratio between treatment and control group for each arm	Proportion succeeding in renewing insurance coverage by date	End of observation period
Coverage gap	Time ratio between treatment and control group for each arm	Mean length in days/duration until renewal	End of observation period
Acceptance of autorenewal option	Odds ratio between treatment and control,	Proportion signing up for autorenewal	End of observation period
Successful renewal via autorenewal	Odds ratio between treatment and control	Proportion of autorenewal set-ups resulting in a successful renewal	End of observation period
User experience and acceptability of intervention	Agreement with questions regarding usefulness and usability of intervention	Proportion of individuals agreeing with statements	Follow-up survey Post-intervention period

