## Participant timeline {13}

### Sample size {14}

We compute sample size estimations for a binary-outcome, parallel group superiority trial assuming 95% significance (α = 0.05), 80% power (β = 0.20), and a normal distribution [25, 26]. In order to account for the clustered randomization, we inflate the sample size estimate with the design effect coefficient [(1 + (n-1) ρ], where n is the cluster size and ρ is the intraclass correlation coefficient [27, 28]. We assume an intracluster correlation coefficient of ρ = 0.2, an average cluster size of n = 1.3 for the verified sample, and n = 1.7 for the unverified number sample based on our estimates of sample characteristics. We conservatively assume an effect size of 10% based on systematic reviews of SMS-based reminder systems in health care settings [14–19, 29, 30]. This gives us a requirement of 2530 individuals per arm. Since the phone number validation exercise showed that 48% of NHIS members did not have their current, up-to-date phone number on file, we must assume that only a fraction of SMS-reminders in the unverified population will reach the intended target, so we can expect smaller effect sizes for the unverified number sample. If unintended spill-overs occur, this could further attenuate effect size. As a result, we chose to randomly select 30,000 phone number clusters into each arm for the unverified number sample. This is the maximum sample size feasible due to budget constraints. With this sample size, an effect size as small as 3.46% would be detectable in the unverified number sample.

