### Assignment of interventions: allocation

#### Sequence generation {16a}

To select the unverified sample, we randomly draw 240,000 phone number clusters from a total of 1,128,542 eligible individuals in the NHIS database who were not already identified during the verification exercise. As phone numbers are frequently re-assigned by the phone companies or passed on to relatives and friends, all unverified individuals with a phone number on file that is shared with someone in the verified sample are excluded to prevent spillovers. We then split our verified and unverified samples into the expiration date groups 1, 2, and 3 as described above. In order to prevent spill-overs between the groups, individuals in the auxiliary groups (2, 3) who share a phone number with an individual in the main group (1) are also removed from the sampling population before randomization. Group 1 is cluster-randomized by phone number into the arms 1R (reminders), 1 A (autorenewal), and 1 C (control) with 1:1:1 proportion. Group 2 are cluster-randomized by phone number into the arms 2R (reminders), 2 A (autorenewal), and 2 C (control) with 1:1:1 proportion. Group 3 is cluster-randomized by phone number into arms 3 A (autorenewal) and 3 C (control) with 1:1 proportion. The randomizr command executed in Stata (15.1) uses a computer-generated sequence to randomly assign treatment by assigning a number between 0 and 2 (for groups 1–2) and 0 and 1 (for group 3) to each individual phone number cluster. The researchers pass on the allocation list with the anonymous unique identifiers to the technical implementation team, which executes the sending of the messages according to this allocation. Researchers do not remain blinded after the allocation has been completed in order to begin monitoring technical functioning and outcomes.

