## Statistical methods

### Statistical methods for primary and secondary outcomes {20a}

Descriptive statistics for each treatment arm at baseline will summarize sociodemographic characteristics as means, percentages, or counts with standard deviations. The primary outcome will be assessed as the difference in renewal rates between each treatment and its corresponding control group, comparing the difference between those who received renewal reminders (1R, 2R) or autorenewal prompts (1A, 2 A, 3 A) against the respective control group (1C, 2 C, 3 C). Specifically, we compare 1R vs. 1 C, 1 A vs. 1 C, 2R vs. 2 C, 2 A vs. 2 C, and 3 A vs. 3C. The primary outcome is rate of successful renewals in each group. The primary endpoint is the effect size, estimated with a logistic regression of treatment status on insurance outcome, and reported as an odds ratios with significance levels (*p* values and 95% confidence intervals). To assess whether reminders resulted in less or in shorter coverage gaps, we will conduct a duration analysis, comparing time-to-renewal between the treatment arms using Kaplan–Meier curves and Weibull regressions. All effect sizes will represent an intent-to-treat (ITT) effect, as we cannot be certain if a treatment reached the intended recipient. The secondary outcomes will be assessed using descriptive statistics and logistic regressions in order to compare the likelihood of signing up for autorenewal, and the likelihood of a successful renewal occurring, conditional on having signed up for autorenewal, across the different expiration date groups. The results will be reported as absolute differences and odds ratios. We cluster-randomize individuals by phone number in order to avoid having individuals with the same phone number in different treatment arms, which could result in spill-overs. For the analysis, we use individual-level analysis for two reasons: (1) because the treatment is addressed to each individual and timed according to individuals’ expiration dates, making this an individual-level treatment, and (2) ~ 85% of phone number clusters contain only one individual, making an application of a mixed-effects model difficult, as there would be nearly as many random intercepts as there are observations. However, we do use clustered standard errors in the analysis to account for possible intra-cluster correlations.

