## Discussion

### Explanation of design choice

The phone numbers of members registered in the NHIS member database are often outdated. As a result, a renewal reminder sent to a number in the data base may not reach the intended recipient. Furthermore, an SMS message may reach an unintended recipient, because members sometimes register with a facilitators phone number (such as a local kiosk owner, NHIS staff, or medical staff), because phone numbers are passed on to friends or relatives, or because phone numbers are re-assigned by the telecommunications company after a period of inactivity. For a subset of 65,000 Kumasi residents, a phone number verification exercise was conducted to assess the magnitude of this problem. For all surveyed members, an up-to-date primary phone number was recorded for each individual. This exercise showed that only 48% of numbers in the data base matched the primary phone number stated by the member. Using this sample of recently verified phone numbers allows us to recruit a group of trial participants with a high likelihood of an SMS message reaching the intended recipient instead of another person (who may be in a different arm of the trial). This will allow for an evaluation with a high internal validity and result in an accurate treatment effect. However, this type of phone number verification exercise is very resource-intensive and may not be scalable to the entire population. Furthermore, the verified number sample was not representative of the member population in Kumasi, as older and female members were more likely to be found in the survey locations during the verification exercise. Therefore, we also draw a random, representative sample from the NHIS data base to test the same intervention at a larger scale in a more realistic setting (excluding all those with phone numbers which were recorded in verified group). This will allow for an evaluation with a high external validity and an intent-to-treat effect. It will also allow us to assess the value of additional information and the necessity of such verification exercises. By combining the two approaches, we are able to evaluate both the effectiveness of the intervention and the potential for scale-up, without having to sacrifice internal or external validity. In the verified number sample, the differently sized treatment arms result from the fact that insurance status and expiration dates are not distributed equally throughout the sample. As a result, Group 1 is the largest, followed by Group 2, while Group 3 is very small. For the unverified number sample, we are able to randomly select individuals from a much larger pool of members in the NHIS database. Here, we chose to randomly draw equally sized Groups 1–3, which will result in equally sized treatment arms.

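### The protocol contradicts itself on the primary outcome: three renewal versions are primary, two of them are also secondary, and the methods name a single undated rate

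*Protocol article*

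**What the plan says.** - **Outcomes {12}, primary table.** There is one row: "Renewal status at end of observation period (renewal by expiration date, renewal without coverage gap, any renewal"). The metric is an odds ratio for each arm, read at the end of the observation period.
- **Outcomes {12}, secondary table.** The first row is "Renewal by expiration date (by t_0_), renewal without coverage gap (by t_90"), with the same metric, method of aggregation and time point.
- **Statistical methods {20a}.** The wording is singular and gives no deadline: "The primary outcome is rate of successful renewals in each group". The comparisons are "1R vs. 1 C, 1 A vs. 1 C, 2R vs. 2 C, 2 A vs. 2 C, and 3 A vs. 3C", each reported with a p value and a 95% confidence interval.
- **Explanation for the choice of comparators {6b}.** Group 2 is made up of members whose insurance had already expired before the intervention. Group 3 expires after the planned end of the intervention.
- **Sample size {14}.** Planning is done "assuming 95% significance (α = 0.05), 80% power (β = 0.20), and a normal distribution", with the verified and unverified samples considered separately.
- **Discussion, Explanation of design choice.** On the unverified sample: "we also draw a random, representative sample from the NHIS data base to test the same intervention at a larger scale".

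**The concern.** An endpoint cannot be both primary and secondary, and a single rate cannot be three rates. The versions are not interchangeable. The abstract reports that 40% of active members have a gap in a given year while 19% do not renew at all. Reminders run from 28 days before expiry to 89 days after it, so they could move the timing of renewal without changing whether it happens, or the reverse. Which version is primary can therefore decide the conclusion.

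The text also does not say which of the five comparisons, or which sample, decides the trial. Section {16a} says that researchers are unblinded after allocation and monitor outcomes. Trial status dates this version to 08 November 2025, after the interventions ended on 31 December 2024. An open choice of primary result at that point weakens whatever is reported as primary.

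**Working it through.** **1. The three statements side by side**

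| Renewal version | Primary table | Secondary table | Section {20a} |
|---|---|---|---|
| By expiry (t0) | primary | secondary | not named |
| Without gap (t90) | primary | secondary | not named |
| Any renewal | primary | not listed | closest to the undated rate |

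Only any renewal has a status that all three places can share.

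**2. Fit to the groups.** For Group 2, t0 lies before the intervention, so renewal by t0 cannot occur in the trial. Group 2 reaches back to expiries on 1 October 2022, so t90 had also passed for members who expired more than 90 days before the start. For Group 3, t0 falls after the intervention, and the text gives no date for the end of observation. The primary row therefore does not fit all five primary comparisons.

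**3. The plan's own figure.** The 2530 per arm can be reproduced with a two-sided alpha of 0.05, 80% power, an *assumed* control rate of 40% and a relative effect of 10% (40% to 44%):

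- Variance term: 0.40 × 0.60 + 0.44 × 0.56 = 0.4864.
- (1.960 + 0.842)² = 7.849.
- 0.4864 × 7.849 / 0.04² = 2386.
- Design effect: 1 + (1.3 − 1) × 0.2 = 1.06, giving 2530 after rounding up.

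The calculation uses one alpha of 0.05, not split.

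**4. Counting the tests.** These counts suppose that each test is done at 5% in both samples, which is an inference.

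- All versions everywhere: 3 × 5 × 2 = 30. This is an upper bound.
- Without t0 in Group 2: (6 + 4 + 3) × 2 = 26.
- Any renewal only in Groups 2 and 3: (6 + 2 + 1) × 2 = 18.
- Any renewal only throughout: 5 × 2 = 10.

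**5. Chance of at least one false significant result when no treatment works.** For k independent tests it is 1 − 0.95^k in either direction and 1 − 0.975^k in favour of treatment. The tests are correlated: comparisons within a group share a control, and the endpoints are nested. For nested rates a < b the correlation is (a − ab)/√[a(1−a)b(1−b)]. A simulation with 400,000 replicates used four *assumed* sets of control rates (t0/t90/any): 50/60/80%, 30/50/60%, 50/55/60% and 40/50/81%.

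| Tests | Independent: either / favourable | Correlated: either | Correlated: favourable |
|---|---|---|---|
| 30 | 78.5% / 53.2% | 57–69% | 34–43% |
| 26 | 73.6% / 48.2% | 54–65% | 32–40% |
| 18 | 60.3% / 36.6% | 47–53% | 26–30% |
| 10 | 40.1% / 22.4% | 38% | 21% |

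**6. Room for a stricter threshold.** Halving alpha to 0.025 scales the sample size by [(2.241 + 0.842)/(1.960 + 0.842)]² = 1.21, so 2530 becomes about 3,060. The strictest step of Holm over five tests (0.01) needs 3,764. Group 1 is the largest of three groups in the verified sample. If the groups total 61,097, it holds at least 61,097/3, or 61,097/9 ≈ 6,800 per arm.

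**The case against.** The strongest reply has three parts.

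- **Multiplicity rules often sit in an analysis plan, and none is shown here.** Five prespecified contrasts of two interventions, in populations expected to respond differently, need not form one error family, and the discussion gives the two samples different purposes. This stands: the absence of an adjustment is not itself the finding. It does not rescue the outcome tables, because an analysis plan cannot make one endpoint both primary and secondary.
- **There is a simple reading.** The undated rate in {20a} fits any renewal, the one version not repeated as secondary. This also stands, and the fix follows it.
- **Stronger conclusions do not follow.** A reader might infer 30 primary tests and a false success more likely than not. Thirty cannot all exist, because Group 2 had already expired. The totals above 50% count harm as well as benefit, whereas a superiority trial succeeds only in favour of treatment. No section says that any one significant result is enough.

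Two further inferences should be resisted. Section {16a} mentions "individuals in the auxiliary groups (2, 3) who share a phone number with an individual in the main group (1"), but that is a rule for removing shared numbers before randomization, not an analysis hierarchy. And the dates in Trial status show that a late choice is possible, not that one was made.

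**Conclusion.** The contradiction is certain and needs no calculation: the two outcome tables and {20a} disagree on what is primary, and the primary row includes an endpoint that cannot occur in Group 2.

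The size of the consequence is conditional. If any significant result at 5% in either sample counted as success, the chance of at least one false result favouring treatment would be about 21% under the singular wording of {20a}, and about 26% to 43% for 18 to 30 tests. In either direction the figures are 38% and about 47% to 69%. A single two-sided 5% test gives 2.5% in favour and 5% in total. The figures assume the control rates listed, shared controls with equal arms, and separate testing of the two samples, which {14} and the discussion imply but {20a} does not state. Well above 5% is supported; a probable false success is not.

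**What to change.** 1. Keep one version as primary. Any renewal by a dated end of observation fits {20a} and is the only version not listed as secondary.
2. List renewal by t0 and by t90 only as secondary, for the groups in which they can occur, and align both outcome tables with {20a}.
3. State which comparison or comparisons, and which sample, decide the primary conclusion. Otherwise report the five comparisons with a Holm adjustment beside the unadjusted results.
4. Because the interventions ended before this version, use the version specified before data access and disclose any later choice.

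Making t90 the primary version and testing the verified sample first is not the natural repair. It would promote an endpoint now listed as secondary, assume follow-up that the text does not date, and add a testing order after the interventions ended.

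Steps 1, 2 and 4 cost only wording and disclosure. Step 3 costs a stricter threshold: about 3,060 per arm for two tests, or 3,764 at the strictest Holm step over five, against roughly 6,800 or more per Group 1 arm in the verified sample. The verified sizes of Groups 2 and 3 are not given in the text, and Group 3 is described as very small, so the same reassurance cannot be given there.

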## Interventions

### Explanation for the choice of comparators {6b}

We break down our samples into 3 groups based on their membership status and expiration dates. Group 1 contains all individuals with active insurance and an expiration date during the intervention period. Group 2 contains all individuals with a currently expired membership and expiration date between 1 October 2022 and the end of the pre-intervention period. Group 3 contains all members with active insurance and an expiration date after the planned end date of our intervention period. We do this because expired members require different reminders and autorenewal messages than active members, and because those with a renewal date during the intervention phase receive messages around their expiration dates which individuals with renewal date outside of this time frame cannot receive. Furthermore, we expect that individuals with expired insurance may react differently than individuals with active insurance, and that those with more imminent renewal dates may respond differently than those whose renewal dates are still far away. We randomly allocate treatment within each group, clustering individuals by phone number to prevent spillovers. Group 3 is only assigned autorenewal or control, because the renewal window opens 90 days before expiration, therefore sending reminders to a group whose insurance expires in 6 months at the earliest would not be sensible.

Due to the randomization, the treatments and control within each expiration date group (1, 2, 3) arms only differ by the treatment status. Individuals in the control arms will not receive SMS prompts for renewal or autorenewal, but will otherwise receive usual communications from the NHIA which are not related to this trial. Only participants assigned to be treated in the autorenewal arm will be able to sign up for the autorenewal platform as primary users, but will be able to add other individuals (typically dependents and other family members) to their renewal plan and pay for their renewals. All other individuals will be able to access the USSD Menu of the autorenewal platform through the short-code, but will not be able to sign up for the service. Instead, they will be shown an error message informing them that this platform is still undergoing testing and may be made available at a later date (Fig. 1).

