### Methods in analysis to handle protocol non-adherence and any statistical methods to handle missing data {20c}

Non-adherence may result from individuals opting out of receiving messages and no longer receiving treatment. To assess the magnitude of non-adherence, we will compare opt-out rates between treatment arms. If opt-outs occur at high or at unequal rates between different treatment arms, an instrumental variable approach which instrumentalizes allocation for realized treatment status will allow for the estimation of an accurate local average treatment effect (LATE) despite non-adherence or technical failures [36]. Another potential source of non-adherence may stem from an autorenewal user from treatment arm A adding an individual from arm R or C to their renewal plan, resulting in a different treatment being administered. Therefore, autorenewal registrations across the different treatment arms will also be monitored. If a non-negligible number of participants is re-assigned thusly, the instrumental variable approach may also be used to account for this type of non-adherence.

Missing data is unlikely to occur as the routine data capture system usually ensures that all relevant routine data is collected automatically. If observations for time-consistent variables are missing from the data, they may be imputed from previous transaction records of an individual. Other missing data will not be imputed.

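### The treatment-versus-control odds ratio set for autorenewal sign-up and autorenewal success has an empty control side by design, and the statistical methods name a different contrast

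*Protocol article*

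**What the plan says.** The table under Secondary outcomes has one row for acceptance of autorenewal and one for successful renewal through it.

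- **Metric, both rows:** "Odds ratio between treatment and control".
- **Aggregation, acceptance:** "Proportion signing up for autorenewal".
- **Aggregation, success:** "Proportion of autorenewal set-ups resulting in a successful renewal". The denominator is therefore set-ups, not members allocated.

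Section {6b} on the choice of comparators restricts access: "Only participants assigned to be treated in the autorenewal arm will be able to sign up for the autorenewal platform as primary users". Everyone else can open the menu "but will not be able to sign up for the service" and is shown an error message. There is one side door: autorenewal-arm users "will be able to add other individuals (typically dependents and other family members) to their renewal plan". Section {20c} lists this route, "adding an individual from arm R or C to their renewal plan", as a source of non-adherence.

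Section {20a} defines the control arms as 1C, 2C and 3C. For sign-up and for success it describes a comparison "conditional on having signed up for autorenewal, across the different expiration date groups", with results given as odds ratios and absolute differences.

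**The concern.** A ratio against control needs a control group in which the event can occur. Here the platform itself prevents sign-up outside the autorenewal arms, so a comparison with control shows only that the block worked. The success outcome is worse placed, because its denominator is made up of set-ups and controls have none of their own.

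The statistical methods section names a different comparator for the same two outcomes. A reader cannot tell which one is planned, and the choice could be made after the data are seen. These rows carry the evidence on uptake and functioning of the autorenewal service, which Objective 2 is about.

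The contrast across expiration date groups can be estimated but needs care on two counts. Allocation is random within Groups 1, 2 and 3, not between them. Also, the success denominator takes in set-ups in 3A whose renewal has not yet been attempted.

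**Working it through.** The plan states no value for either odds ratio, so there is no figure to reproduce. The check is whether each ratio can be formed.

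**Inputs.** Controls cannot sign up as primary users ({6b}). The size of 30,000 per arm is the number of phone clusters per arm in the unverified sample ({14}), used here as a round number of members. Sign-up rates of 1%, 5% and 20% in the autorenewal arm are assumptions, since the document gives none.

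**Sign-up.** With *a* sign-ups among n₁ in the autorenewal arm and *c* among n₀ controls, OR = [a/(n₁ − a)] / [c/(n₀ − c)].

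- By design c = 0. At 5%, a = 1,500 and the ratio is (1,500/28,500)/(0/30,000) = 0.0526/0, which has no finite value. The same holds at any uptake above zero.
- A logistic regression on these data separates. At 10, 20 and 35 iterations the coefficient is 8.3, 18.8 and 19.9, with standard errors 1.6, 304 and 539.
- Adding 0.5 to each cell gives 607, 3159 and 15001 at 1%, 5% and 20% sign-up. With the control cell at zero, these values depend on the constant chosen.

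**Success among set-ups.** Controls have 0 set-ups, so their proportion is 0/0 and the ratio is undefined.

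**If added controls are counted as signed up** (5% sign-up in the autorenewal arm, odds 1,500/28,500 = 0.0526):

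| Controls added | Control odds | OR |
|---|---|---|
| 1 | 1/29,999 | 1579 |
| 10 | 10/29,990 | 158 |
| 50 | 50/29,950 | 31.5 |
| 300 | 300/29,700 | 5.2 |

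Acceptance in the autorenewal arm is identical in every line. The ratio moves only with spill-over into control.

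**Group 3.** Autorenewal fires 30 days ahead of expiry, or the day after sign-up if expiry is closer than that (Treatment 2: Autorenewal). Group 3 is defined by expiry after the planned end of the intervention ({6b}). Let *f* be the share of 3A set-ups whose trigger date has passed by the end of observation, and *s* the success rate once triggered. With all set-ups in the denominator, as the table row reads, the reported proportion is f × s. It understates *s* whenever f < 1. The document gives neither the expiry distribution in Group 3 nor the length of the observation period, so *f* cannot be computed.

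**The case against.** The strongest reply is that {20a} already contains a workable analysis: descriptive statistics and logistic regression across expiration date groups, where sign-up is possible in 1A, 2A and 3A. This stands. A reader might infer that the planned model cannot converge, but separation affects only the table's contrast with control.

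A reader might also infer that both ratios are undefined whatever happens. That goes too far. The block is on primary users, and {18a} extracts autorenewal registration status for every participant. If added controls appear there as registered, finite ratios can be computed. They would still not measure acceptance.

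Spill-over is also not overlooked. Section {20c} plans to monitor registrations across arms and offers an instrumental-variable analysis. What is missing is only a statement that such registrations are kept out of the acceptance outcome.

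For Group 3 it is tempting to attach a number. Suppose expiry is spread evenly over the six months after the intervention and true success is 90%. Then f = 1/6 and the reported figure is 15% if observation stops with the intervention. If it runs one, two or three months longer, f is 2/6, 3/6 or 4/6 and the figure is 30%, 45% or 60%. The spread, the 90% and the cut-off are all assumptions, so none of these figures is a finding. The exact denominator is also something an analysis plan may settle. The direction of the effect does follow from the text.

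Finally, {20a} makes no causal claim for the comparison across groups, so labelling it non-randomised is a clarification, not the correction of an error.

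**Conclusion.** The metric in two of the five secondary outcome rows is wrong as written and conflicts with {20a}. Leaving aside controls added by others, the sign-up odds ratio has a zero denominator at any positive uptake, and the success odds ratio has 0/0 on the control side. With added controls counted, the ratio is finite but reflects non-adherence. This follows from the access rule in {6b} and needs no assumed figure. The numerical illustrations rest on 30,000 per arm and assumed sign-up rates.

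The understatement of success in 3A is a matter of direction only, and it applies if untriggered set-ups stay in the denominator.

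A reader might take this as a threat to the trial's main conclusion. It is not: the primary outcome is renewal, which can occur in every arm, and the randomised comparisons for it are untouched. The proportions named in the table's aggregation column also remain estimable within the autorenewal arms. This is an inconsistency in secondary uptake outcomes that should be corrected before they are reported.

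**What to change.** 1. In both table rows, replace the metric with the proportion within each of 1A, 2A and 3A (sign-up; success among set-ups), with 95% confidence intervals clustered by phone number.
2. In {20a}, keep the comparison across Groups 1 to 3 and state that it is non-randomised.
3. Report control and reminder members added to someone else's plan separately, as non-adherence under {20c}, and exclude them from acceptance.
4. Alongside success among all set-ups, give success among set-ups whose trigger date has passed by the end of observation, and state when observation ends.

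The cost is the wording of two table rows and a sentence or so of methods, and the analysis becomes simpler. The extract described in {18a} already holds trial arm, registration status, platform used, transaction date and insurance period dates. The opt-in date is not listed there and would be needed for set-ups made within 30 days of expiry or after it. The interventions ended on 31 December 2024, so the change concerns analysis and reporting only and should be recorded as a dated clarification.
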